| | Discuss the research design including but not limited to such issues as: probability of group assignment, potential for subject to be randomized to placebo group, use of control subjects, etc. | | --- | | |  | Twenty participants will complete procedures during treatment with placebo and study medication, in random order, using a within-subjects, double-blind, placebo-controlled design. There will be a two week period between each phase. The dose of doxazosin needed to alter the effects of cocaine is unknown and preclinical animal studies have not been conducted. Because of this, initially we will study the effects of a low dose of doxazosin (4mg daily) compared to placebo daily. Because this class of medication needs to be titrated upward due to the potential for hypotension, treatment will begin at 1mg and increased by 1mg increments every three days until 4mg is reached. Placebo will be dosed identically. Blood pressure (resting and orthostatic) will be assessed daily prior to dosing. Cocaine (0, 20, and 40mg) will be administered during treatment with 4mg doxazosin/placebo. On day 10, cocaine will be administered in ascending dose (20mg followed by 40mg) with the 0mg dose randomly interspersed to maintain the blind. Cardiovascular measures and subjective effects ratings will be assessed following cocaine administration. Participants will be monitored for stability on days 11 and 12 and discharged from the hospital on day 13. Discharge will only occur for subjects who have a supine BP of 100/65 mm Hg or higher, a seated blood pressure of 90/60 mm Hg or higher, and an orthostatic change upon standing of < 20 mm Hg systolic or < 10 mm Hg diastolic.  If 4mg doxazosin treatment is well tolerated but is not associated with alterations in the effects of cocaine, a second group of subjects will be studied using the same sample size. Treatment will begin at 1mg and increased by 1mg increments every three days until 8mg is reached. All study procedures will be identical as described above. Placebo will be dosed identically. | | --- | --- | | |

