| | Inclusion Criteria: | | --- | | |  | 1. Be English-speaking volunteers who are not seeking treatment at the time of the study; 2. Be between 18-55 years of age; 3. Meet DSM-IV TR criteria for cocaine dependence; participants may or may not meet criteria for nicotine dependence. Nicotine dependence is allowed but not required because most cocaine users smoke cigarettes. 4. Have a self-reported history of using cocaine by the smoked or IV route; 5. Have vital signs as follows: supine blood pressure > 100/65 mm Hg, a seated blood pressure of > 90/60 mm Hg and < 150/90 mm Hg, and an orthostatic change < 20 mm Hg systolic or <10 mm Hg diastolic on standing. Resting pulse must be < 90 bpm. 6. Have hematology and chemistry laboratory tests that are within normal (+/- 10%) limits with the following exceptions: a) liver function tests (total bilirubin, ALT, AST, and alkaline phosphatase) < 3 x the upper limit of normal, and b) kidney function tests (creatinine and BUN) within normal limits; 7. Have a baseline EKG that demonstrates clinically normal sinus rhythm, clinically normal conduction, and no clinically significant arrhythmias; 8. Have a medical history and brief physical examination demonstrating no clinically significant contraindications for study participation, in the judgment of the admitting physician and the principal investigator. | | --- | --- | | |

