| | Exclusion Criteria: | | --- | | |  | 1. Meet DSM IV TR criteria for dependence on drugs other than cocaine or nicotine. 2. Have any history or evidence suggestive of seizure disorder or brain injury; 3. Have any previous medically adverse reaction to cocaine, including loss of consciousness, chest pain, or epileptic seizure; 4. Have neurological or psychiatric disorders, such as: • psychosis, bipolar illness or major depression as assessed by MINI; • organic brain disease or dementia assessed by clinical interview; • history of any psychiatric disorder which would require ongoing treatment or which would make study compliance difficult; • history of suicide attempts within the past year and/or current suicidal ideation/plan; 5. Have evidence of clinically significant heart disease or hypertension, as determined by the PI; 6. Have evidence of untreated or unstable medical illness including: neuroendocrine, autoimmune, renal, hepatic, or active infectious disease; 7. Have symptomatic HIV or are taking antiretroviral medication; 8. Be pregnant or nursing. Other females must either be unable to conceive (i.e., surgically sterilized, sterile, or post-menopausal) or be using a reliable form of contraception (e.g., abstinence, birth control pills, intrauterine device, condoms, or spermicide). All females must provide negative pregnancy urine tests before study entry, upon hospital admission, and at the end of study participation; 9. Have asthma or currently use theophylline or other sympathomimetics; 10. Have any other illness, condition, or use of psychotropic medications, which in the opinion of the PI and/or the admitting physician would preclude safe and/or successful completion of the study.  Criteria for Discontinuation Following Initiation Participants will be discharged if they have a positive breath test indicating use of alcohol or a urine test indicating illicit use of drugs while in the MED-VAMC, if they do not comply with study procedures, or if they do not tolerate the study drugs. Stopping criteria are detailed below.  Stopping Criteria Cocaine administration will not be initiated if there are clinically significant arrhythmias or if vital signs are outside of acceptable ranges, which are resting pulse < 130 bpm and blood pressure below 165mm Hg systolic and 100mm Hg diastolic. In addition, repeated doses of cocaine will not be administered (and the study physician will halt continued cocaine delivery) if there are behavioral manifestations of cocaine toxicity (agitation, psychosis, inability to cooperate with study procedures).   Stopping Criteria for Further Participation Subject participation will be terminated if any of the following events occur: 1. Systolic BP greater than 180 mm Hg sustained for 5 minutes or more; 2. Diastolic BP greater than 120 mm Hg sustained for 5 minutes or more; 3. Heart rate greater than (220 – age x 0.85) bpm sustained for 5 minutes or more. Note: if a single value exceeding the values above is detected, the readings will be repeated until it is determined whether or not the stopping criteria have been met.  Subject Selection Criteria Rationale Route of administration. Participants are required to have used cocaine by the IV or smoked route to avoid exposing participants to drugs by routes of administration that produce more intensive interoceptive effects than usually used by the participants. Prior experience with smoked cocaine is allowed (rather than restricting the population to those with experience with IV cocaine) because smoked cocaine reaches brain sites of action as rapidly as does intravenously administered cocaine and smoked cocaine produces effects that are comparable to IV cocaine. Speed of administration (and rate of delivery to brain) of stimulant drugs likely impacts subjective and cardiovascular effects, so smoked and intravenously administered cocaine produce similar subjective effects (22-26). | | --- | --- | | |

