| F2.  Procedure |
| |  | | --- | | |  | Screening Interested candidates will receive an explanation of the study purpose and requirements. If still interested, the candidates will be allowed to review, inquire about, and sign the study informed consent form. After providing informed consent, subjects proceed to the screening assessment phase of the study. A urine drug toxicology screen will be conducted for drugs of abuse. Some of this sample will be shared with Rice university to develop new tests for drug detection. A saliva sample will also be collected for this purpose. Candidates deemed eligible based on initial screening assessments will be administered a MINI by a trained mental health professional, to determine if there are any psychiatric conditions that might exclude the potential subject from participation. Blood will be collected for analysis of hematology and chemistry tests. These assessments must be completed within 14 days before intake. At the initial screening visit, restrictions on use of alcohol, drugs of abuse, and medications will be reviewed. All subjects will be required to sign a written statement that they will abstain from use of cocaine or other psychostimulants throughout the duration of their participation in the trial.  All applicants for study participation will receive counseling as part of their participation, and will be advised that treatment for drug abuse is indicated and available. Applicants not participating in the study will receive treatment referral information as appropriate. At completion of their participation, study subjects will again be advised that treatment is indicated and available, and will be given treatment referral information and assistance.  Participants will reside on the Research Commons for the duration of the study (about 28 days total). Participants must refrain from illicit and prescription drug use, and we will confirm compliance by urine testing and breath alcohol level testing. Passes and monitoring. Passes will not usually be allowed, and visitors will not be permitted. Participants’ belongings will be searched upon arrival.  The study schedule outlined below may change by a day or two due to scheduling issues and/or safety reasons. We will ask participants to complete the protocol twice (once being randomized to placebo and once being randomized to doxazosin, but this wont be required.   General Procedures: Participants will be studied while residing on the Research Commons. Cocaine administration sessions will be conducted at approximately the same time of day for a given participant. Experimental sessions will be several hours in duration and will be conducted in a quiet room with research and medical staff present. The room will contain an experimental station, equipped with a response console attached to a personal computer and video monitor. Heart rate, EKG, and blood pressure will be recorded throughout experimental sessions using an automatic monitoring system.   Smoking, caffeine, and food. Caffeine and food will be prohibited during and 90 min before study sessions excepting a 1 hour break for lunch.   Day 1-10: The study participants will be randomized to receive either doxazosin or placebo. Doxazosin treatment will begin at 1mg and will be increased by 1mg increments every three days until 4mg is reached. Placebo will be dosed identically. Prior to dosing doxazosin, and at 1 hour intervals after each dose from hours 2 through 6 after dosing, sitting and supine orthostatic blood pressure will be assessed.  Cardiovascular monitoring and discontinuation criteria For doxazosin to be administered, the following criteria must be met: 1. supine blood pressure above 100/65 mm Hg, 2. a seated blood pressure of above 90/60 mm Hg, 3. and an orthostatic change smaller than 20 mm Hg systolic or smaller than 10 mm Hg diastolic on standing. The dose will not be increased until the participant has met criteria for dosing and has received 3 doses at a given dose level.  a. Participants who do not meet the criteria above at any time during hours 2 through 6 after dosing will remain supine until the next BP assessment. b. Participants who do not meet the criteria above consistently from hours 2 through 6 after any dosing will not have their dose of doxazosin increased and will remain at the prior dosing level. c. Participants who do not meet the requirements for dosing increase (supine blood pressure > 100/65 mm Hg, a seated blood pressure of > 90/60 mm Hg, and an orthostatic change < 20 mm Hg systolic or <10 mm Hg diastolic on standing) for 6 days will have medication discontinued and they will be discontinued from the study.   Day 10: Cocaine 20mg, 40mg and matched placebo saline will be administered via IV push by the study physician on day 10, at hourly intervals, with the placebo dose randomly interspersed to maintain the blind. To ensure that subjects will not be at risk from cocaine, the resting pulse must be < 90 bpm and the blood pressure must be < 150 mmHg systolic and < 90 mmHg diastolic immediately prior to dosing. Heart rate and blood pressure measurements will be made prior to cocaine dosing and at 15-minute intervals thereafter until 30 minutes following the final dose. Visual-analogue scale ratings of “any cocaine effect”, “high”, “good effects”, “bad effects”, “like cocaine”, “desire cocaine”, “depressed”, “anxious”, “stimulated”, and “if you had access to cocaine right now, how likely would you be to use it?” will be collected at -15 min, 5 min, 10 min, 15 min, 20 min, 30 min, and 45 min after cocaine dosing. Participants will remain seated during experimental sessions except for brief visits to the lavatory.   All infusions will be administered in single-blind fashion. All experimental procedures will be conducted in a hospital room located in the GCRC. Infusions will be administered over 2 minutes by I.V. push. Vital signs must remain within values specified under Stopping Criteria for initiation of cocaine administration. An ACLS-certified physician will be present from 15 min before drug administration until at least 1 hour after cocaine administration. The physician will be available in house and on pager for at least 4 hours after drug administration. Heart rate will be measured using continuous ECG from 15 min prior to cocaine or placebo dosing until 2 hours after dosing. Blood pressure will be assessed at frequent intervals from 15 min prior to cocaine or placebo dosing until 2 hours after dosing.   Discharge Participants will be monitored for stability on days 11 and 12 and discharged from the hospital on day 13. Discharge will only occur for subjects who have a supine BP of 100/65 mm Hg or higher, a seated blood pressure of 90/60 mm Hg or higher, and an orthostatic change upon standing of < 20 mm Hg systolic or < 10 mm Hg diastolic. Prior to discharge subjects will have a physical examination and vital signs, and complete the Beck Depression Inventory-II. An assessment of adverse events will be completed.  Participants will have the choice of returning two weeks later to complete study procedures.   Stopping Rules Doxazosin Participants who do not meet the criteria listed above (supine blood pressure above 100/65 mm Hg, a seated blood pressure of greater than 90/60 mm Hg, and an orthostatic change smaller than 20 mm Hg systolic or smaller than 10 mm Hg diastolic on standing) at any time during hours 2 through 6 after dosing will remain supine until the next BP assessment. Participants who do not meet the criteria above consistently from hours 2 through 6 after any dosing will not have their dose of doxazosin increased and will remain at the prior dosing level. Participants showing syncope or dizziness that does not respond to sitting down will be discharged from the study.  Stopping Criteria for Further Participation Participants who do not meet the requirements for dosing increase for 6 days will have medication discontinued and they will be discontinued from the study.  Cocaine Cocaine will not be administered if there are clinically significant arrhythmias or if vital signs are outside of acceptable ranges, which are resting pulse below 90 bpm and blood pressure below 150mm Hg systolic and 90mm Hg diastolic. In addition, repeated doses of cocaine will not be administered (and the study physician will halt continued cocaine delivery) if there are behavioral manifestations of cocaine toxicity (agitation, psychosis, inability to cooperate with study procedures).   Stopping Criteria for Further Participation Subject participation will be terminated if any of the following events occur: 1. Systolic BP above 180 mm Hg sustained for 5 minutes or more; 2. Diastolic BP above 120 mm Hg sustained for 5 minutes or more; 3. Heart rate above (220 – age x 0.85) bpm sustained for 5 minutes or more. Note: if a single value exceeding the values above is detected, the readings will be repeated until it is determined whether or not the stopping criteria have been met.  Adverse event assessment and management. We will assess participants’ well-being daily. Spontaneously reported symptoms or complaints will be recorded and reported to the IRB and NIDA and the FDA if events are classified as serious. Specific guidelines have been developed to guide assessment and intervention in the event of cardiovascular toxicity, such as malignant hypertension, ventricular arrhythmia, chest pain, etc., and are in use for our other studies involving cocaine administration. These guidelines are intended to support rather than supersede clinical judgment. If needed, a code team responds. Participants needing to be transferred to a medical or ICU ward can be, though this has never been necessary.   Assessments see attached | | --- | --- | | |

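### The vital-sign check before each cocaine infusion sets upper limits only and omits the seated 90/60 floor that the protocol uses at entry, before each doxazosin dose and at discharge

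*Protocol*

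**What the plan says.** Vital-sign limits for giving cocaine appear three times in the protocol.

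- Section F2, Day 10, immediately before dosing: "the resting pulse must be < 90 bpm and the blood pressure must be < 150 mmHg systolic and < 90 mmHg diastolic".
- Section F2, Stopping Rules, Cocaine: the acceptable range is "resting pulse below 90 bpm and blood pressure below 150mm Hg systolic and 90mm Hg diastolic".
- Section F1, Stopping Criteria (after the exclusion criteria): the acceptable range is "resting pulse < 130 bpm and blood pressure below 165mm Hg systolic and 100mm Hg diastolic".

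A lower limit for seated pressure appears at three other points.

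- Inclusion criterion 5: "a seated blood pressure of > 90/60 mm Hg and < 150/90 mm Hg".
- Section F2, criteria for giving doxazosin: "a seated blood pressure of above 90/60 mm Hg".
- Discharge (Sections F1 and F2): "a seated blood pressure of 90/60 mm Hg or higher".

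Section F1 explains the slow dose increase: "Because this class of medication needs to be titrated upward due to the potential for hypotension". Section H1 lists both a rise and a fall in blood pressure among the risks of cocaine, and promises strict go/no-go criteria for the infusions. The Day 10 text gives the purpose of its limits as protecting participants from risk due to cocaine.

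**The concern.** The Day 10 check repeats the ceilings of inclusion criterion 5 (seated pressure 150/90, pulse 90) but not the floor beside them. Cocaine is given during treatment with a drug that lowers pressure, and nominally on the first day at the target dose. The primary objective is the safety of that combination, judged by hemodynamic and subjective effects. If the check is to be the strict gate that Section H1 promises, a reading too low for doxazosin should not pass it unremarked.

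At stake is whether the decision to infuse at a low seated pressure follows a written rule, applied alike in both phases, or is left to discretion on the day.

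**Working it through.** No power or sample-size figure is involved. The check is a comparison of the thresholds, followed by a count of the infusions concerned.

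**Thresholds against one reading.** Take an illustrative (assumed) participant without symptoms or arrhythmia, seated pressure 86/54, pulse 85.

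| Decision | Seated pressure and pulse limits | Result |
| --- | --- | --- |
| Entry (F1, inclusion 5) | above 90/60, below 150/90; pulse below 90 | Fails: 86 and 54 are under the floor |
| Doxazosin dose (F2) | above 90/60 | Fails |
| Discharge (F1, F2) | 90/60 or higher | Fails |
| Cocaine, Day 10 and Cocaine rule (F2) | below 150/90; pulse below 90 | Passes: 86 < 150, 54 < 90, 85 < 90 |
| Cocaine, Stopping Criteria (F1) | below 165/100; pulse below 130 | Passes: 86 < 165, 54 < 100, 85 < 130 |

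The F1 and F2 ceilings disagree with each other. That is a separate matter; the floor is missing from both sets.

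**Other rules that might supply a floor.**

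- F2 says that vital signs at infusion must stay within the stopping criteria. Those are ceilings.
- Participation ends on sustained systolic pressure above 180, diastolic above 120, or a high heart rate. These are also upper limits only.
- The pre-dose doxazosin check does apply the floor, but before doxazosin, not before each infusion.
- Failing the doxazosin criteria 2 to 6 hours after a dose leads to lying down until the next reading, to no dose increase if the failure is consistent, and to discontinuation if the criteria for an increase are not met for 6 days. None of these mentions cocaine.
- Syncope, or dizziness not relieved by sitting down, leads to discharge from the study. A participant without symptoms is not covered.

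So nothing in the visible text makes an infusion conditional on a minimum pressure.

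**Timing.** With 1 mg steps every three days, the nominal schedule is 1 mg on days 1-3, 2 mg on days 4-6, 3 mg on days 7-9 and 4 mg on day 10, the day of the cocaine session. The protocol lets the schedule move by a day or two.

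**Number of infusions concerned**, assuming that 20 participants complete both phases and reach 4 mg:

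- active cocaine on doxazosin: 20 x 2 = 40;
- saline on doxazosin: 20 x 1 = 20;
- all infusions in the placebo phase: 20 x 3 = 60;
- checks to which a uniform floor would apply: 40 + 20 + 60 = 120.

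If the conditional 8 mg group is run with the same sample size, it adds another 20 x 2 = 40 active infusions on doxazosin. These are planned totals, not estimates of how many would be given at low pressure.

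**The case against.** The strongest reply is that ceilings suit the purpose of this check. Section H1 describes cocaine as a strong sympathomimetic and links illicit use to myocardial infarction and stroke, so the expected danger is high pressure. The floor sits with the drug that lowers pressure. Different limits for different drugs are not a contradiction. This stands in part: the protocol does not contradict itself here. But Section H1 also names lowered pressure as a cocaine risk, and the effect of the combination is what the study sets out to learn.

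It can also be said that the gap is narrow. Each doxazosin dose already requires the floor, pressure is read hourly from hours 2 to 6 afterwards, those who do not tolerate the study drugs are discharged, and the study physician gives each infusion in person. This stands as a limit on likely frequency. It does not supply a written minimum.

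A reader might infer that cocaine could be infused while a participant is under the order to lie down after doxazosin. The documents do not support going that far. The interval from dose to session is not given, so overlap with hours 2 to 6 is not established, and the rule that participants stay seated in sessions makes the order a partial hold in practice.

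Finally, the cardiovascular-toxicity guidelines and the Section H monitoring form are not shown. The finding concerns the visible text.

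**Conclusion.** The point holds as a gap in the written check and should be fixed. All three statements of the cocaine limits are ceilings only, so cocaine may be infused at a seated pressure at which the protocol would neither give doxazosin nor discharge the participant.

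A reader might go further and conclude that the protocol exposes participants to a known danger, or that 40 infusions are unsafe. Neither follows. The document does not show that 20 or 40 mg is more harmful at low seated pressure, and it gives no basis for estimating how often such a reading would occur. The 40 is a denominator and rests on 20 two-phase completers at 4 mg. In practice the second phase is optional, and some participants may be held below 4 mg. Nor can it be said that the trial has no working lower limit anywhere, since some safety documents are not shown.

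The conclusion rests on the wording of the thresholds and does not depend on the illustrative reading.

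**What to change.** Add a seated blood pressure above 90/60 mm Hg to the check immediately before every infusion, saline included and identically in both phases. Put it in the two F2 statements of the limits (Day 10 and the Cocaine stopping rule), and carry it to the F1 Stopping Criteria for consistency. If the floor is not met, delay the infusion until repeat readings meet it. State how long the wait may last before the infusion counts as withheld, and whether 40 mg may be given when 20 mg was not. Report delayed and withheld infusions by phase.

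The cost in procedure is amendment wording. No measurement is added, because "Heart rate and blood pressure measurements will be made prior to cocaine dosing and at 15-minute intervals thereafter".

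The cost in data is an occasional delayed or withheld infusion, probably more often on doxazosin. One withheld infusion loses 1 of 20 pairs (1/20 = 5%) at that dose. Because active doses ascend, a withheld 20 mg dose may also forgo the 40 mg dose, losing 1 of 20 pairs at each. Such missing data would depend on low pressure under doxazosin, so the infusions that remain would come from participants with higher pressure. The hemodynamic results should therefore be presented together with the counts of delayed and withheld infusions. More frequent delays in one phase could also hint at the allocation; a uniform rule limits this but does not remove it.

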| | Distribution Plan: | | --- | | |  | Participants will be paid $40 in gift certificates for the completion of the screening. The payment schedule is shown below. $50 is the average compensation provided for each day, however, compensation increases over the course of the study to make up for the increasing difficulty participants may have abstaining from illicit cocaine use. If a participants leaves the study early, payment will be prorated.   Day 0 - $20 Day 1 - $20 Day 2 - $25 Day 3 - $30 Day 4 - $35 Day 5 - $40 Day 6 - $45 Day 7 - $50 Day 8 - $55 Day 9 - $60 Day 10 - $80 Day 11 - $100 Day 12 - $50 Day 13 - $50 total $660  In addition, participants will receive an extra $40 on Monday, which can be any study day, depending on the day of entry.This is to compensate for staying over the weekend. Payment on Day 11 is larger to serve as a study completion bonus. Subjects completing both phases will receive $1400 plus a $100 bonus. | | --- | --- | | |
|  |
| Section M:  Genetics |
| | How would you classify your genetic study? | | --- | | |  | DNA diagnostic study | | --- | --- | | |

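### Back-loaded pay is prorated with no stated exception for safety removal, which gives participants a financial reason to under-report dizziness and may bias reported tolerability

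*Protocol*

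**What the plan says.** **Payment (Section L, Distribution Plan).** Daily amounts rise from $20 on days 0 and 1 to $100 on day 11, and the list ends "Day 10 - $80 Day 11 - $100 Day 12 - $50 Day 13 - $50 total $660". The reason given for the rise is that "compensation increases over the course of the study to make up for the increasing difficulty participants may have abstaining from illicit cocaine use". In addition, "participants will receive an extra $40 on Monday". On completion: "Payment on Day 11 is larger to serve as a study completion bonus. Subjects completing both phases will receive $1400 plus a $100 bonus". On early exit: "If a participants leaves the study early, payment will be prorated". The plan does not say whether leaving covers removal by the study, and it draws no line between reasons for leaving.

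**Removal.** Section F1 (Criteria for Discontinuation Following Initiation) puts drug use, non-compliance and not tolerating the study drugs in one sentence. Section F2 (Stopping Rules, Doxazosin) adds: "Participants showing syncope or dizziness that does not respond to sitting down will be discharged from the study".

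**Symptom recording (Section F2, Adverse event assessment and management).** Well-being is assessed daily, and "Spontaneously reported symptoms or complaints will be recorded". An adverse event assessment also takes place before discharge.

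**Use of tolerability (Section F1, Design).** A second group titrated to a higher dose is opened if 4 mg is well tolerated but does not alter the effects of cocaine.

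**The concern.** Whether dizziness persists after sitting down is known mainly from what the participant says. Saying so can end participation, and as Section L is worded that also ends pay, with the better-paid days still to come. Section J2 states that advertisements are aimed at users interested in taking part for money, so pay is a real motive in this population.

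At stake is reported tolerability, meaning dizziness and similar complaints. If it is under-reported, 4 mg looks better tolerated than it is, and the second-group decision leans toward opening. If doxazosin causes more dizziness than placebo, under-reporting in both phases also shrinks the observed difference. The stated reason for the rising schedule, abstinence from cocaine, gives no ground for withholding pay from someone removed for an effect of the study drug.

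**Working it through.** **1. Reproduce the plan's totals (Section L).**
- Days 0 to 13: 20 + 20 + 25 + 30 + 35 + 40 + 45 + 50 + 55 + 60 + 80 + 100 + 50 + 50 = $660, as stated.
- With one Monday payment: 660 + 40 = $700 per phase, or 700/14 = $50 a day, as stated.
- Both phases: 2 × 700 = $1,400; plus $100 bonus = $1,500; plus $40 screening = $1,540. All match.

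**2. Loss within one phase by day of removal.** Prorating is read as payment of the listed amount for each day up to and including the day of removal. Loss = 660 − cumulative pay; share = loss/660. If each dose level is held three days, the steps fall on days 1, 4, 7 and 10.

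| Day of removal | Earned | Given up | Share of $660 |
|---|---|---|---|
| 1 | $40 | $620 | 94% |
| 4 | $130 | $530 | 80% |
| 7 | $265 | $395 | 60% |
| 8 | $320 | $340 | 52% |
| 9 | $380 | $280 | 42% |
| 10 | $460 | $200 | 30% |
| 11 | $560 | $100 | 15% |

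The loss exceeds half of the phase through day 8 and is below half from day 9.

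**3. Adding the second phase.** For someone who intends both phases, removal in phase 1 also gives up 700 + 100 = $800. Against the $1,500, counting the Monday $40 consistently:
- Phase 1, day 7: 1,500 − (265 + 40) = $1,195 (80%) if the Monday payment was already made; 1,500 − 265 = $1,235 (82%) if not.
- Phase 1, days 1 to 10: 67% to 97%.
- Phase 2, days 1 to 10, after $700 from phase 1: 20% to 51%.

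Section F2 makes the second phase optional, so the $800 does not apply to everyone.

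**4. Could the other monitoring stand in for reported dizziness?**
- Blood pressure is taken before each dose and hourly at hours 2 to 6. But Section C describes prazosin treatment with no change in blood pressure from pretreatment, in which 9 of 14 on prazosin and 6 of 15 on placebo reported transient dizziness on standing and none reported syncope. It says that doxazosin's side-effect profile closely resembles prazosin's. Reported dizziness can therefore arise where group blood pressure has not moved.
- The visual-analogue ratings are timed around cocaine dosing on day 10, and no listed item asks about dizziness.
- The adverse event assessment before discharge comes after the dose steps and the cocaine session.

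These measures are sound for what they measure, but none replaces a daily symptom report during titration.

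**The case against.** Four stronger readings are tempting. The protocol supports none of them.

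- **That symptoms are recorded only when volunteered.** The protocol does not say only. It provides a daily well-being assessment and an adverse event assessment before discharge, and Section H1 has participants told to report adverse experiences at once. The list of assessments and the monitoring plan are attachments that are not shown, and a symptom checklist may exist there. The payment gap in Section L would stand even so.
- **That removal costs most of the payment.** This is true through day 8 of a single phase, or in phase 1 for someone intending both. It is false from day 9 of a phase and for nearly all of phase 2. Days already completed are paid.
- **That the trial pays people to conceal its main outcome.** The stated purpose of the schedule is abstinence. The primary objective in Section D rests on hemodynamic and subjective effects of cocaine doses, which are measured or rated on schedule. Syncope can be observed.
- **That concealment gets a participant past the safety checks.** Dose increases and cocaine dosing depend on measured vital signs, and cocaine also on the absence of arrhythmia. Silence about dizziness does not bypass those checks.

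It is also fair to say that ordinary dizziness is not itself a named trigger, and that failing the blood pressure criteria leads to removal only after 6 days. The unrelieved-dizziness rule and the general intolerance rule remain, and both depend at least partly on self-report.

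The last objection concerns the remedy: paying in full on any claimed symptom would reward leaving early. That is right, and the fix has to be limited accordingly.

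**Conclusion.** The concern stands in a limited form. Section L prorates a rising schedule without an exception for safety or tolerability removal, while a mainly self-reported symptom triggers discharge and the stated recording method is spontaneous report. This gives a reason to under-report dizziness and may bias reported tolerability, and so the second-group decision, toward tolerability.

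The incentive is $530 (80%) on day 4 and $395 (60%) on day 7 of a $660 phase, falling to 30% on day 10. A further $800 applies only to those intending a second phase. The size of any resulting bias cannot be estimated from the protocol.

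The conclusion assumes that leaving early includes removal by the study, that prorating pays the listed amounts for completed days, and that each dose level is held three days. The attached assessments and the consent pages could not be checked.

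**What to change.** 1. **Section F2.** At the existing daily well-being assessment, ask a fixed question about dizziness and faintness in both the doxazosin and placebo phases. Base the tolerability summary that informs the second-group decision in Section F1 on those answers. If the attached assessments already contain such a question, cite it here. This step is worth making on its own.
2. **Section L and the consent form.** State that prorating applies to voluntary departure and to removal for drug use or non-compliance. State also that a removal decided and documented by the study physician on safety or tolerability grounds does not reduce that phase's scheduled pay.

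**Cost.** One question a day and some payment wording. Extra pay is at most $620 per safety removal (day 1). Section G1 plans up to 30 enrolled for 20 completers, so for ten non-completers it is at most 10 × 620 = $6,200, or 10 × 530 = $5,300 if all are removed on day 4. It is about double if a second group opens on the same payment schedule.

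**Limits.** Some incentive to claim symptoms remains, held down by requiring the physician's documented decision. The $800 tied to the optional second phase is untouched: for a day 7 removal in phase 1 that is 800/1,195 = 67% of what is at stake, so the fixed question matters more than the payment wording. No dosing or stopping rule changes.
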